### Trial design {8}

This study is part of the larger DAWn consortium. The DAWn-Antico study is an adaptive, randomized, parallel-group open-label multicenter clinical trial to evaluate the safety and efficacy of promising agents in hospitalized adult patients diagnosed with COVID-19. The study is a phase 2 proof-of-concept multicenter trial program in patients with COVID-19. The adaptive study design of DAWn allows for the addition of new treatment and strata during the study based on the most updated information.

With a 2:1 randomization, the DAWn-Antico study evaluates standard thromboprophylaxis (low molecular weight heparin (LMWH) at 50 IU/kg once daily in hospitalized patients and twice daily in patients on intensive care units) with a multi-step antithrombotic and anti-inflammatory strategy (Fig. 2). This strategy consists of the following:
A.A higher prophylactic dose of subcutaneous LMWH: 50 IU/kg twice daily in hospitalized patients and 75 IU/kg twice daily in patients on intensive care units from day 0 to 15, ANDB.Aprotinin 2 × 10^6^ KIE 4 times per day as intravenous (IV) infusion from day 0 to 3 for a total of 72 h (3 × 4 doses)C.Additionally, patients with biochemical signs of hyperinflammation at baseline or during follow-up will receive add-on interleukin-1 receptor blockage by anakinra 100 mg 4× daily. Hyperinflammation is defined as an absolute lymphocyte count < 1000 cells/mL and two of the following: (1) ferritin > 800 ng/mL, (2) LDH > 400 U/L, or (3) D-dimers > 1000 ng/mL.

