#### Treatment of hyperinflammation

Patients in the intervention arm will be monitored for hyperinflammation. If, at any point during the study, the patient develops signs of hyperinflammation, treatment with anakinra will be started if there are no contraindications (see the “Exclusion criteria” section).

Presence of hyperinflammation is defined as follows:
Absolute lymphocyte count < 1000 cells/mLTwo of the following: (i) ferritin > 800 ng/mL, (ii) LDH > 400 U/L, or (iii) D-dimers > 1000 ng/mL

These lab values have been identified as independent predictors of adverse outcome in patients with severe COVID-19 [2, 4, 22, 23].

Anakinra will be administered by IV infusion at a total dose of 400 mg per day, divided into 4 doses 100 mg IV every 6 h. Anakinra treatment will continue for 15 days, i.e., days 1 to 15. Before administration, the full content of the prefilled, single-use syringe (anakinra 100 mg) will be diluted in 100 mL saline. The IV administration of anakinra has to occur immediately after the preparation over an infusion period of 60 min. Full instructions for the preparation of anakinra are available in the IMP manual. Conditions for storage and injection are described in the attached protocol.

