## Statistical methods

### Statistical methods for primary and secondary outcomes {20a}

#### Analysis of the primary efficacy endpoint

The primary endpoint will be analyzed using competing risk analyses whereby death without any improvement will be considered as a competing risk. Event rates will be estimated using cumulative incidence functions (CIF). Median times to improvement will be calculated by the treatment group.

The effect of treatment will be assessed by performing a Fine and Gray competing risk regression model that includes the baseline clinical status value on day 0 as a covariate and randomized treatment as a factor. From the Fine and Gray model, the treatment effect and associated 95% confidence interval will be estimated.

In the pilot phase of DAWn-Antico, the effect of modulation of thromboinflammation will be evaluated on a laboratory primary efficacy endpoint, mean D-dimer level at day 6. The null hypothesis being tested is that the mean D-dimer level on day 6 is the same for the standard of care and intervention arm. Means will be compared with appropriate statistical testing after checking for normality. The full statistical analysis plan will be finalized before the database lock.

To evaluate the effect of aprotinin and high-dose enoxaparin vs. anakinra, analyses will be performed separately in patients with or without signs of hyperinflammation (i.e., with or without an indication for anakinra in the intervention group).

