### Methods for additional analyses (e.g., subgroup analyses) {20b}

To evaluate the effect of aprotinin and high-dose enoxaparin vs. anakinra, analyses will be performed separately in patients with or without signs of hyperinflammation at randomization (i.e., with or without an indication for anakinra in the intervention group).

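### The split by hyperinflammation can show the whole strategy's effect by baseline state, but not anakinra against aprotinin and LMWH; one of its two statements also omits the time point

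*Protocol article*

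**What the plan says.** The protocol article describes the split in two places.

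- *Analysis of the primary efficacy endpoint*: "To evaluate the effect of aprotinin and high-dose enoxaparin vs. anakinra, analyses will be performed separately in patients with or without signs of hyperinflammation", explained in brackets as whether anakinra would be indicated in the intervention arm. No time point is given.
- *Methods for additional analyses {20b}*: "analyses will be performed separately in patients with or without signs of hyperinflammation at randomization", with the same explanation in brackets about an indication for anakinra.

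Both give the same purpose: "To evaluate the effect of aprotinin and high-dose enoxaparin vs. anakinra".

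On how anakinra is given:

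- *Trial design {8}*: "patients with biochemical signs of hyperinflammation at baseline or during follow-up will receive add-on interleukin-1 receptor blockage by anakinra".
- *Treatment of hyperinflammation*: "If, at any point during the study, the patient develops signs of hyperinflammation, treatment with anakinra will be started", unless contraindicated. The same section says: "Patients in the intervention arm will be monitored for hyperinflammation".
- The Abstract (Methods) describes anakinra as an addition to the other intervention drugs, not an alternative to them.

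Hyperinflammation requires a low lymphocyte count plus two of three raised markers: ferritin, LDH and D-dimer. *Analysis of the secondary endpoint(s)* also lists developing hyperinflammation, and the time to it, among the outcomes. Day-6 D-dimer is the pilot's primary endpoint (*Outcomes {12}*).

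**The concern.** There are two separate problems.

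First, the stated purpose is a comparison of treatment components, but only the package is randomized. If the subgroup results are read as the purpose invites, a stronger or weaker effect in hyperinflamed patients would be credited to anakinra, when it could equally reflect how sicker patients respond to aprotinin and LMWH.

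Second, the two statements of the split differ on timing. An indication for anakinra can arise at any point in the study. If the primary endpoint section were followed to the letter, patients could be classified by hyperinflammation that appears after treatment has started. The trial itself counts that state as an outcome, and D-dimer is both one of its criteria and the pilot endpoint. Comparisons within such groups are no longer protected by randomization.

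**Working it through.** The plan gives no figure for this analysis, so there is none to reproduce. The main argument is structural. The calculations in steps 3 and 4 are illustrative.

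**1. What each subgroup estimates, with a baseline split**

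On any additive effect scale, let:

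- S1, S0 = effect of LMWH + aprotinin versus standard care in patients with and without baseline hyperinflammation;
- A1 = added effect of anakinra in those with baseline hyperinflammation;
- L0 = added effect of anakinra started later in those without it.

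Then:

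- effect in the subgroup with hyperinflammation = S1 + A1;
- effect in the subgroup without = S0 + L0;
- difference between subgroups = A1 + (S1 − S0) − L0.

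The trial yields two estimates for four unknowns. The difference equals A1 only if S1 = S0 and L0 = 0. The documents support neither condition: *Treatment of hyperinflammation* calls the laboratory criteria independent predictors of adverse outcome, and it allows anakinra to start at any time. The comparison actually named, anakinra against aprotinin and LMWH, would be A1 − S1, and only the sum S1 + A1 is estimated. No arm receives anakinra alone, and no hyperinflamed patients are randomized to the strategy with or without it. An indication is also not the same as receipt, because contraindications apply.

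**2. The two timing statements side by side**

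| Section | Time of classification |
|---|---|
| Analysis of the primary efficacy endpoint | not stated |
| Methods for additional analyses {20b} | "with or without signs of hyperinflammation at randomization" |

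The wording is otherwise nearly the same. Only the second statement rules out a classification made after treatment begins.

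**3. What a post-randomization split could do (assumed inputs)**

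Simulation of 4,000,000 patients, allocated 2:1, with no treatment effect on improvement. The inputs do not come from the documents:

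- severity U is standard normal;
- baseline hyperinflammation if U + standard normal noise > 0.8 (28.6% of patients);
- new hyperinflammation: logit = −0.3 + U − e × (intervention);
- improvement: logit = 0.2 − U.

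Differences in improvement, intervention minus control, in percentage points:

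| e | Ever hyperinflamed, intervention / control | Among ever | Among never |
|---|---|---|---|
| 0 | 54.8% / 54.8% | −0.06 | 0.02 |
| 0.5 | 48.1% / 54.8% | −1.64 | −1.15 |
| 1.0 | 42.5% / 54.7% | −3.24 | −2.15 |
| 1.5 | 38.0% / 54.8% | −4.72 | −3.06 |

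With the split at baseline, every difference lay within 0.15 points of zero, and the overall difference was within 0.1. Under ever/never grouping both groups look worse on intervention, because treatment moves intermediate patients from one group to the other.

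**4. The D-dimer criterion alone**

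*Sample size {14}* assumes a mean of 1000, an SD of 600 and a difference of 500. Assume a lognormal distribution, with log-SD = √ln(1 + CV²) and log-mean = ln(mean) − log-SD²/2.

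- Mean 1000, SD 600: log-SD = √ln(1.36) = 0.555; P(>1000) = 39%.
- Mean 500, same CV (SD 300): log-SD 0.555; P(>1000) = 6%.
- Mean 500, SD kept at 600: log-SD = √ln(2.44) = 0.944; P(>1000) = 11%.

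This shows only that one criterion would respond to an effect of the size the pilot seeks. It is not the proportion classified as hyperinflamed.

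**The case against.** The strongest reply is that the timing is already settled. The section devoted to additional analyses says at randomization and carries the same bracketed reference to an indication for anakinra, so that phrase need not mean an indication arising later. Nowhere does the article say that patients will be grouped by follow-up values, and later hyperinflammation is treated as an outcome. This largely stands. A reader might infer that the trial will condition on a post-randomization state. The documents do not support that, only that one of two statements would permit it.

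A second reply is that the analyses are performed separately within subgroups, and that no test between subgroups is written. With a baseline split, each is a valid randomized comparison of the strategy with standard care. This also stands, so it would be wrong to say that the plan compares non-comparable groups. It does not rescue the stated purpose, which appears in both sections and which no later analysis plan can make estimable.

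Two further inferences go too far. The drop from 39% to between 6% and 11% is not a difference in group membership: D-dimer is neither necessary nor sufficient for hyperinflammation, and the drop assumes the pilot's full day-6 effect. The sentence naming only the intervention arm as monitored does not show that hyperinflammation goes unrecorded in controls. It describes the trigger for anakinra, while the secondary analyses report hyperinflammation without restriction to an arm.

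Finally, the form of a subgroup model is commonly left to the analysis plan. Its absence is not part of this point; it appears only in the remedy.

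**Conclusion.** The point holds on two counts, of unequal weight.

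The stated aim is unattainable. This follows from the design and needs no numerical assumption: anakinra is a non-randomized add-on, so neither subgroup effect nor their difference isolates it or sets it against aprotinin and LMWH.

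The missing time point is an inconsistency to reconcile. A baseline split was probably intended. If the looser statement were followed, spurious differences of roughly 1 to 5 percentage points could arise with no true effect. That size rests wholly on the assumed severity model and on an assumed treatment effect on new hyperinflammation.

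The primary Fine and Gray analysis, the pilot test of day-6 D-dimer and the sample size are not affected. What changes is what the trial may conclude about its components. It should be corrected before the analysis plan is finalized.

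**What to change.** 1. In *Analysis of the primary efficacy endpoint*, add that hyperinflammation is classified at randomization, so that it matches *Methods for additional analyses {20b}*. Define it from laboratory values taken before the first dose, applied identically in both arms.
2. In both sections, restate the aim as the effect of the whole strategy versus standard care in patients with and without baseline hyperinflammation.
3. Compare the two effects through a treatment-by-baseline-hyperinflammation interaction in one model, and report both subgroup effects with 95% confidence intervals.
4. Drop any claim about anakinra versus aprotinin and LMWH. Later hyperinflammation remains an outcome, as already planned.

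The cost is a wording change in two sections and one model term. Treatment and recruitment do not change. The trial gives up only a conclusion that its design cannot support.

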#### Analysis of the secondary endpoint(s)

Cumulative clinical status up to day 15 will be analyzed using a general linear model adjusted for clinical status on day 0. The treatment effect will be estimated by the difference of mean values between the groups.Cumulative clinical status recorded daily during the hospital stay and on days 15 and 19 will be analyzed using a proportional odds logistic regression model, adjusted for clinical status on day 0. The common odds ratio will estimate the treatment effect.All-cause mortality rates will be estimated by the treatment group using the Kaplan-Meier method. The resulting Kaplan-Meier curves will be compared using a log-rank test. The treatment effect will be estimated by the hazard ratio using a Cox regression.Time-to-event parameters with competing risk (time to clinical improvement, composite cardiac endpoint): event rates will be estimated using cumulative incidence functions (CIF), and the resulting CIF curves will be compared using Gray’s test. The subdistribution hazard ratio will estimate the treatment effect.Duration of hospital and ICU stay: both parameters will be analyzed as time-to-event parameters with competing risk, whereby the event of interest is discharged from hospital/ICU, and the competing risk is hospital/ICU death.Continuous normally distributed variables (e.g., QTc) will be analyzed using a 2-sample *t* test. Treatment effects will be estimated by the difference in mean values between the groups. If applicable, changes from baseline will be calculated. Comparisons between treatment groups will be made by performing an analysis of covariance (ANCOVA) on the post-baseline value, using the baseline value as a covariate.Continuous non-normally distributed variables (clinical status, NEWS score, duration of supplemental oxygen, duration of mechanical ventilation) will be analyzed using a Wilcoxon rank-sum test. Change in ordinal scale at specific time points will be compared using Wilcoxon rank-sum tests.The proportion of patients with D-dimer < 1000, ferritin < 1000, and LDH < 600 on day 6 and day 15 will be compared.The proportion of patients who develop hyperinflammation at days 3, 6, and 15; time to hyperinflammation.

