### Sample size {14}

Sample size estimates provided serve as a reference, but not as an indication of the final number of patients to be randomized.

In the pilot phase of DAWn-AntiCo, we will evaluate the effect of modulation of the thromboinflammatory response on biochemical parameters. To evaluate the effect of this strategy, we will evaluate the difference in mean D-dimers on day 6. Published data show highly variable D-dimer values in patients with COVID [2, 3]. For an estimated mean D-dimer of 1000 with a standard deviation of 600, a sample size of 51 patients (17:34 with 1:2 randomization) has a power of 0.8 and an alpha of 0.05 to detect a difference of 500. We will therefore evaluate the effect of the intervention after a pilot phase of 60 (20:40) patients. Based on the information from other DAWn studies, the final sample size for effect on clinical outcomes will be evaluated following this pilot phase.

In their study comparing clinical improvement rates for lopinavir-ritonavir in hospitalized patients with severe COVID-19, Cao et al. reported a clinical improvement rate in the control group of 37.7% on day 14 [25].

Therefore, for our sample size calculations, we assume that a 40% improvement rate will be observed on day 15 in the control group, which yielded an expected hazard ratio of 1.5632. Since all missing clinical status data up to day 15 will be imputed, we assumed no censoring of the data prior to day 15. Based on the log-rank test, with a 2-sided significance level of 5% and 80% statistical power and using a (2:1) randomization ratio in favor of the intervention, we estimate that a total sample size of 354 patients will suffice to detect an absolute improvement of 15% (i.e., 55% in the intervention group). To detect an absolute improvement of 20% (60% in the intervention group), a total sample of 196 patients will suffice. We propose a pragmatic sample size of 210 patients taking into account early dropouts.

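### The mortality comparison names no adjustment for day 0 clinical status, although the primary model does; the test is valid but less efficient than it could be

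*Protocol article*

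**What the plan says.** In the protocol article, under Analysis of the secondary endpoint(s), all-cause mortality is estimated by Kaplan-Meier in each arm. Then: "The resulting Kaplan-Meier curves will be compared using a log-rank test". No stratification of that test is mentioned. The next sentence reads "The treatment effect will be estimated by the hazard ratio using a Cox regression", with covariates neither listed nor excluded.

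Elsewhere the article names the adjustment where it wants it. Under Analysis of the primary efficacy endpoint, the Fine and Gray model "includes the baseline clinical status value on day 0 as a covariate". In the same list as mortality, the first item reads "Cumulative clinical status up to day 15 will be analyzed using a general linear model adjusted for clinical status on day 0", and the proportional odds analysis that follows is adjusted for the same value.

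Three other places bear on the point. Outcomes {12} promises every outcome both overall and separately by baseline severity (mild/moderate against severe). Sections {16a} to {16c} on allocation name no stratification factor. Trial design {8} and section {20a} leave the analysis plan to be finalized before database lock.

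**The concern.** The inclusion criteria admit patients on radiographic infiltrates alone as well as patients on mechanical ventilation. Day 0 status can therefore run from category 3 (in hospital without oxygen) to category 6 (invasive ventilation or ECMO) of a 7-point scale on which category 7 is death. It is reasonable to expect this value to predict death, although the documents do not say how strongly.

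A plain log-rank test ignores that information. If day 0 status is prognostic, the test has less power than one that uses it. A severity difference between arms that arises by chance also passes straight into the hazard ratio. At 210 patients the smaller arm has 70, so such differences need not be small. Mortality would then be analysed on a different footing from the primary endpoint, which does use the covariate.

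**Working it through.** **1. The plan's own figure.** The only sample size for a time-to-event comparison concerns clinical improvement, not death. Sample size {14} states: "we assume that a 40% improvement rate will be observed on day 15 in the control group, which yielded an expected hazard ratio of 1.5632". It works "with a 2-sided significance level of 5% and 80% statistical power and using a (2:1) randomization ratio in favor of the intervention".

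- Hazard ratio: ln(1 - 0.55)/ln(1 - 0.40) = 1.5632.
- Schoenfeld events: (1.960 + 0.842)²/[(1/3)(2/3)(ln 1.5632)²] = 7.849/(0.2222 × 0.1996) = 177.
- Mean event rate at 2:1: (0.40 + 2 × 0.55)/3 = 0.50. N = 177/0.50 = 354.

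This agrees with the statement that "a total sample size of 354 patients will suffice to detect an absolute improvement of 15% (i.e., 55% in the intervention group"). For 60% against 40% the same steps give a hazard ratio of 1.794, 104 events and N of 194-195, against the stated 196. The figures reproduce, and none of them depends on the mortality analysis.

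**2. Power of the planned mortality test.** Assumed: N = 210 at 2:1, mortality hazard ratio 0.5, control mortality m. The article calls its sample sizes a reference and not the final number, so 210 is itself an assumption. Deaths = 210 × [m/3 + 2(1 - (1 - m)^0.5)/3]; power = Φ(√(deaths × 2/9) × |ln 0.5| - 1.96).

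- m = 10%: 14.2 deaths, power 23%.
- m = 20%: 28.8 deaths, power 42%.
- m = 30%: 43.9 deaths, power 58%.

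**3. Gain from using day 0 status.** Simulation, 2,000 trials per row. Assumed: 28 days of follow-up, exponential times, four baseline levels held by 10/50/20/20% of patients, and a constant death hazard ratio per level. The adjusted Cox model enters the level as a score, which matches how the data were generated and so favours adjustment somewhat.

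| N | Control mortality | Death HR per level | Log-rank | Unadjusted Cox | Adjusted Cox | Median HR, unadjusted / adjusted |
|---|---|---|---|---|---|---|
| 210 | 20% | 1 | 0.463 | 0.451 | 0.448 | 0.51 / 0.50 |
| 210 | 30% | 1 | 0.642 | 0.629 | 0.627 | 0.50 / 0.50 |
| 210 | 20% | 2 | 0.458 | 0.445 | 0.462 | 0.52 / 0.50 |
| 210 | 30% | 2 | 0.588 | 0.579 | 0.635 | 0.52 / 0.50 |
| 210 | 20% | 3 | 0.417 | 0.399 | 0.479 | 0.53 / 0.50 |
| 210 | 30% | 3 | 0.527 | 0.517 | 0.642 | 0.55 / 0.50 |
| 354 | 20% | 2 | 0.659 | 0.649 | 0.680 | 0.51 / 0.50 |
| 354 | 20% | 3 | 0.625 | 0.616 | 0.681 | 0.53 / 0.49 |

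A second simulation with the same N, allocation, treatment effect and mortality range gave, for log-rank against adjusted Cox, 0.45 v 0.47 and 0.59 v 0.65 at a death hazard ratio of 2 per level, and 0.42 v 0.48 and 0.49 v 0.62 at 3 per level. Across both, at N = 210, the gain is about 0-6 points at 2 per level and 6-13 points at 3 per level. With no prognostic effect there is no gain.

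**4. Type I error.** With no treatment effect, N = 210 and 20% control mortality, the log-rank test rejected in 4.9% and 5.0% of trials (2 and 3 per level) and the adjusted Cox model in 4.5% and 4.2%.

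**5. Chance imbalance.** Assume 20% of patients are ventilated on day 0. With 140:70, the standard deviation of the between-arm difference is √[0.2 × 0.8 × (1/140 + 1/70)] = 5.9 percentage points. A gap of at least 10 points is 10/5.9 = 1.7 standard deviations, which occurs in about 9% of trials. If ventilated patients had four times the death hazard (assumed), 25% against 15% ventilated would shift the crude hazard ratio by roughly (1 + 3 × 0.25)/(1 + 3 × 0.15) = 1.75/1.45, about 1.2-fold.

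**The case against.** The case for leaving the text alone is substantial.

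- **The planned test is valid.** A reader might infer that omitting the covariate biases the comparison or forfeits the balance that randomization gives. It does neither. Balance holds in expectation, the error rate of the test already allows for chance imbalance, and the null simulations confirm about 5%. This stands in full.
- **The article does not call the Cox model unadjusted.** It lists no covariate, and a condensed article may leave that to the full protocol or the analysis plan. That is correct: for the Cox model, no adjustment is an inference from the contrast with neighbouring items. The log-rank test is different. It is the stated comparison, and as written it takes no account of day 0 status. The silence on stratified randomization may likewise be filled by the full protocol.
- **Severity is shown elsewhere.** Presenting outcomes by baseline severity would make an imbalance visible. It would not adjust the overall hazard ratio or its p-value.
- **The unadjusted hazard ratio of 0.51-0.55 is not evidence of error.** A reader might take it as dilution of a true 0.50. It is largely the expected gap between a marginal and a conditional hazard ratio, so adjustment also changes what is estimated.
- **Mortality has no special rank or power claim.** Secondary hypotheses are tested non-hierarchically, and other secondary analyses (Gray's test, t tests, Wilcoxon tests) also omit day 0 status. This limits the weight of the point but does not remove the advantage of using a covariate already in hand.

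**Conclusion.** The point holds as a minor matter of efficiency and consistency. The stated mortality test uses no baseline information, while the primary model and both cumulative status analyses use day 0 clinical status. Under the assumptions shown, the cost at 210 patients is about 0-6 points of power if the death hazard doubles per baseline level, about 6-13 points if it triples, and none if status is not prognostic. The hazard ratio is also open to chance severity differences.

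The documents supply no mortality rate, case mix or prognostic strength, so no single figure within that range can be defended. Adjustment would not rescue power: in these scenarios mortality stays below 80% at 210 patients either way. The documents do not support reading this as an invalid analysis, and no conclusion on the primary endpoint depends on it.

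**What to change.** In the analysis plan, before database lock, name day 0 clinical status as a covariate in the mortality Cox model. Take the treatment p-value either from that model or from a log-rank test stratified by day 0 status, and state in advance which of the two it is. If the stratified test is chosen, add a rule for merging levels with few deaths. Keep the Kaplan-Meier curves as description. Age, already in the imputation model of section {20c}, may be added as an option.

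The cost is one line of wording and no new data. The reported hazard ratio becomes conditional on baseline status, so the unadjusted hazard ratio should be given beside it as supportive. Because the trial is open-label, the choice should be fixed before outcomes by arm are examined. No alpha or sample size changes.
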